#### SBT failure criteria

SBT failure will be documented in the electronic case report form (eCRF) if the patient develops any of the following:

Worsening oxygenation (SpO_2_ <90% with FiO_2_ ≥50%).Acute distress (respiratory rate≥40 /min, agitation, cyanosis).Haemodynamic instability (systolic blood pressure ≤90 or ≥180 mm Hg, heart rate >140 /min or increase of 20%.Change in mental status.

#### Extubation

Following a successful SBT, extubation should be considered eligible for extubation if the following conditions are met:

Completed a successful SBT (patient did not meet any of the failure criteria listed above).Cooperative cognitive state, as determined by the treating physician.Adequate cough, as determined by the treating physician.Frequency of suctioning is greater than every 2 hours.

The decision to extubate remains however at the discretion of the treating intensivist. Prophylactic intervention, including non-invasive ventilation, high flow nasal cannula, or both, should be considered for patients meeting any of the following criteria:

≥65 years of age.Underlying cardiac disease.Underlying respiratory disease.

The study protocol does not mandate specific reintubation criteria but requires documentation of all reintubation events.

### Intervention description

#### Levosimendan

After randomisation, subjects will receive either levosimendan or a placebo at a starting dose of 0.1 µg/kg/min,^17^,^19^ diluted with glucose 5%. Use of an initial bolus of levosimendan is generally not recommended, mostly to minimise the risk of vasodilation.^20^ In absence of rate limiting effects (heart rate >130/min, hypotension defined as mean arterial blood pressure (MAP) <65 mm Hg, infusion rate is increased after 4 hours to 0.2 µg/kg/min for the remaining 20 hours. If the patient has rate-limiting side effects at the dose of 0.2 µg/kg/min infusion rate is reduced to 0.1 µg/kg/min or less or even discontinued.^6 21^ This dosage will be repeated weekly until successful weaning from invasive ventilator or until the primary endpoint is reached, with a maximum of four doses administered.

#### Placebo

The placebo group will receive intravenous multivitamins (Soluvit N) as a placebo. When diluted (10 mL in 500 mL glucose 5%), Soluvit N provides a yellow colour that matches the characteristic appearance of levosimendan. This is consistent with practices in other intervention trials with levosimendan,^22^,^25^ LevoHeartShock (NCT04020263). The route, volume and infusion rate are matched with the administration of levosimendan to maintain blinding during the study.

### Criteria for discontinuing or modifying allocated interventions

Study medication (levosimendan or placebo) will be administered intravenously at a starting rate of 0.1 µg/kg/min, with the option to increase to 0.2 µg/kg/min after 4 hours if well tolerated. If a patient develops haemodynamic instability, defined as a heart rate >130 beats/min or hypotension with mean arterial pressure <65 mm Hg, the infusion rate will be reduced to 0.1 µg/kg/min or lower, or discontinued altogether if necessary or if requested by the patient. Any discontinuation of treatment will be documented in the electronic case report form, including the underlying reason.

### Strategies to improve adherence to interventions

To ensure adherence to the study protocol, each study site will have a dedicated team trained by the steering committee. Training will include an initiation visit, review of standard operating procedures (SOPs), and a clinical lesson for all nurses and physicians involved in the trial. Additionally, the research pharmacy will receive an SOP for proper preparation and blinding of study medications. ICU nurses will also receive an SOP on infusion rates and when to adjust dosages, with close monitoring of both adjustments and side effects.

The weaning process will be standardised as much as possible, with daily assessments by the intensivist to determine whether SBT criteria are met.

Any deviations from the study protocol will be documented in the eCRF and evaluated during data safety monitoring board (DSMB) meetings.

### Relevant concomitant care permitted or prohibited during the trial

Treating physicians may prescribe any concomitant medications or treatments deemed necessary to provide adequate patient care without restrictions due to this research. Vasopressors, inotropes and antiarrhythmic medications will be considered relevant medications and must be recorded in the eCRF.

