### Clinical trial rationale

Respiratory muscle weakness frequently develops in invasively ventilated patients and is strongly associated with adverse clinical outcome.^3 7^ Respiratory muscle weakness in ventilated patients is partly explained by muscle atrophy,^8^ but also by impaired force generation at a given intracellular calcium concentration, that is, a so-called reduced calcium sensitivity of contraction.^9^ Reduced calcium sensitivity reduces contractile efficiency, that is, more energy is needed and more CO_2_ is generated as compared with non-ICU patients. Levosimendan is a cardiac inotrope that improves calcium sensitivity of force generation of cardiac muscle and is approved for treatment of acute heart failure. Regarding the diaphragm, research followed a stepwise approach to investigate the effects of levosimendan on diaphragm function, progressively moving from basic to clinical studies. First, levosimendan improved the calcium sensitivity of force generation in diaphragm fibres.^4^ This was the very first study to demonstrate that pharmacological modulation of the troponin complex improves human diaphragm function. Second, in a double-blind placebo-controlled trial in healthy subjects, levosimendan improved in vivo contractile efficiency of the diaphragm by 21%.^5^ Levosimendan also restored diaphragm contractility after loaded breathing (reversal of muscle fatigue). Third, in a double-blind placebo-controlled study, we demonstrated that levosimendan increased tidal volume, minute ventilation and decreased arterial CO_2_ in critically ill ventilated patients.^6^ No serious adverse events occurred. In summary, previous work demonstrated that respiratory muscles of invasively ventilated patients show impaired calcium sensitivity of contraction and that levosimendan improves calcium sensitivity. Given these results, we hypothesise that levosimendan shortens the weaning process by enhancing respiratory muscle function, ultimately leading to a reduced ICU length of stay and lower mortality rates compared with standard care.

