### Eligibility criteria

Patients are eligible for participation in WEANLESS if: (1) admitted to a participating ICU; (2) aged 18 years or older; (3) invasively ventilated for more than 48 hours and (4) have at least one failed separation attempt (a failed SBT or failed extubation). The following exclusion criteria have been defined: pre-existing neuromuscular disease, endotracheally intubated primarily for neurological reason, treatment with intermittent haemodialysis, treatment limitation decision in place: do not reintubate, previous treatment with levosimendan within 30 days, currently in another interventional trial or contraindications for levosimendan. Contraindications for levosimendan are: severe renal failure (creatinine clearance <30 mL/min) unless managed with continuous appropriate kidney replacement therapy (such as continuous veno-venous haemofiltration (CVVH)), severe liver failure (Child-Pugh class C), history of torsade des pointes; known significant mechanical obstructions affecting ventricular filling/outflow or both; prolonged QTc interval (QTc >470 ms); pregnancy, breast feeding; known hypersensitivity to levosimendan. See figure 1 for the enrolment procedure.

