### Data collection and management

#### Plans for assessment and collection of outcomes

Most study data will be collected from electronic patient records, ensuring accurate and efficient documentation. Baseline characteristics will be recorded on enrolment, including demographic data, medical history, Acute Physiology And Chronic Health Evaluation II (APACHE II) and Sequential Organ Failure Assessment (SOFA) scores, ECG, medication use, intoxication and baseline laboratory. If a cardiac echocardiogram is performed as part of standard care to evaluate potential weaning failure,^27^ data on ejection fraction and diastolic function will be collected. However, if a cardiac ultrasound is not performed as part of standard care, no additional ultrasound will be conducted for study purposes.

Clinical parameters including ventilator settings, respiratory mechanics, haemodynamic status and laboratory values will be recorded daily until day 28 or ICU discharge. Blood samples will be collected in selected centres to assess the pharmacokinetics of levosimendan in critically ill patients. Baseline NT-proBNP measurements will be used to identify patients with a cardiac origin of weaning failure. Pharmacokinetic assessments will be conducted at 24, 48, 72 and 120 hours after completion of the first dose of the study medication. While blood sampling will be performed in most patients, logistical constraints may prevent its feasibility in all participating hospitals, meaning not all patients will undergo these assessments.

Dyspnoea scores will be assessed using a standardised daily dyspnoea scale. The score will only be evaluated in patients with a Richmond Agitation-Sedation Scale score between −2 and +2, and in the absence of delirium or confusion as determined by the confusion assessment method for the intensive care unit (CAM-ICU) assessment. After confirming adequate mental status using two trigger questions, patients will be asked whether they are experiencing dyspnoea. If they confirm the presence of dyspnoea, a visual analogue scale (VAS) ranging from 0 to 10 will be used to quantify its severity. The EuroQol 5-dimensions 5-level questionnaire is a standardised instrument to describe and value health, consisting of a descriptive system and a VAS. The EQ-5D-5L will be performed at baseline (describing the situation before ICU admission), after 3 months and after 12 months.

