### Statistical methods

#### Statistical methods for primary and secondary outcomes

For data analysis, an intention-to-treat analysis will be performed on the primary outcome, with patients analysed according to their assigned treatment arms, except for cases lost to follow-up, or patients who are withdrawn due to lack of deferred informed consent. Statistical uncertainty will be expressed by the 95% confidence levels with p value under 0.05 will be considered statistically significant.

The primary analysis of the primary outcome, which is ventilator-free days up until day 28 (VFD-28), will reflect a composite endpoint combining both mortality and the duration of ventilation. This approach integrates the impact of death (assigned a value of 0 VFD) and the length of time a patient remains on invasive ventilation. Day 0 will be defined as the day of randomisation, with the duration of intubation prior to randomisation reported as a baseline variable. The individual components of the composite endpoint, mortality rates and the duration of ventilation, will be described separately for both treatment groups to provide detailed insights into the effects of the intervention. The primary analysis for VFD-28 will use a cumulative logistic regression model to account for the ordinal nature of the endpoint. This model will estimate ORs and 95% CIs to quantify the effect of the treatment compared with the control group.

A pre-planned secondary analysis will be conducted focusing on patients with cardiac failure. This analysis will specifically assess this subgroup to explore potential differential effects of treatment. Patients with cardiac failure will be identified using a baseline NT-proBNP level.

A full statistical analysis plan will be made available before the closing of the database.

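### The concomitant-care rule makes no exception for non-study levosimendan after randomisation and does not say to stop the blinded infusion if it is given

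*Protocol article*

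**What the plan says.** All references are to the protocol article.

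- **Relevant concomitant care permitted or prohibited during the trial** gives the only rule on other drugs: "Treating physicians may prescribe any concomitant medications or treatments deemed necessary to provide adequate patient care without restrictions due to this research". It then adds: "Vasopressors, inotropes and antiarrhythmic medications will be considered relevant medications and must be recorded in the eCRF". Inotropes are thus drugs to be written down, not drugs to be avoided.
- **Clinical trial rationale** places the test drug in that class: "Levosimendan is a cardiac inotrope that improves calcium sensitivity of force generation of cardiac muscle and is approved for treatment of acute heart failure".
- **Eligibility criteria** exclude "previous treatment with levosimendan within 30 days". This looks back from entry, and nothing carries it past randomisation. Heart failure is not an exclusion.
- **Statistical methods** and **Methods for additional analysis** both plan an analysis of patients with cardiac failure, so such patients are expected in the trial.
- **Levosimendan** (intervention description) sets 0.1 µg/kg/min for 4 hours, then 0.2 for the remaining 20 hours if tolerated. On repeats: "This dosage will be repeated weekly until successful weaning from invasive ventilator or until the primary endpoint is reached", up to four doses.
- **Criteria for discontinuing or modifying allocated interventions** reduces or stops the infusion on a clinical trigger: "If a patient develops haemodynamic instability, defined as a heart rate >130 beats/min or hypotension with mean arterial pressure" below 65 mm Hg. Starting non-study levosimendan is not a trigger.

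**The concern.** The section does more than stay silent. It grants an open permission, and on a plain reading that permission covers the test drug in both arms. The sponsor already treats outside levosimendan as important enough to exclude patients who had it in the 30 days before entry. Yet all study dosing, pharmacokinetic sampling and outcome measurement come after randomisation, where no limit applies.

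Three things are at stake, in this order:

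1. **Safety in the active arm.** The physician does not know the allocation. Open-label levosimendan could be added to a running infusion of the same drug, and the dose-reduction rule responds only once heart rate or blood pressure has changed.
2. **Treatment contrast.** Use in the placebo arm is crossover. It may appear in the inotrope record, but because it is permitted it would not be logged as a protocol deviation.
3. **Pharmacokinetics.** The article states: "Pharmacokinetic assessments will be conducted at 24, 48, 72 and 120 hours after completion of the first dose of the study medication". In an affected patient those levels could not be attributed to the study dose alone.

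**Working it through.** **1. Does any other section close the gap?**

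| Safeguard | What it does | What it leaves open |
|---|---|---|
| Inotropes recorded in the eCRF | Documents use | Does not discourage it |
| 30-day exclusion | Acts at entry | Nothing after randomisation |
| Rate reduction for heart rate >130 or MAP <65 | Acts on a haemodynamic change | Not triggered by starting the drug |
| Emergency unblinding | Available where allocation is critical for safety | Not linked to open-label use |
| DSMB review of deviations and of threats to validity | Can look at use afterwards | Permitted use is not a deviation |
| Intention-to-treat analysis | Keeps the comparison as randomised | Does not affect dosing |

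None of these says what to do with the study infusion when non-study levosimendan is started.

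**2. Dose stacking.** The planned maximum rate is 0.2 µg/kg/min. The non-study rates are assumptions.

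- 0.2 + 0.1 = 0.3, and 0.3 / 0.2 = 1.5 times the maximum.
- 0.2 + 0.2 = 0.4, and 0.4 / 0.2 = 2 times the maximum.
- One full study infusion delivers 0.1 × 240 min + 0.2 × 1200 min = 24 + 240 = 264 µg/kg.
- Simultaneous infusion is possible for at most 4 × 24 = 96 hours per patient.

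**3. Pharmacokinetic window.** A 24-hour infusion plus 120 hours gives 144 hours from the start of the first infusion to the last sample.

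**4. The plan's own sample size.** The inputs from the sample size section are a difference of 3.9 days (25% of 15.6), SD 10.6 and two-sided alpha 0.05.

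- n = 2 × (1.960 + 0.842)² × 10.6² / 3.9² = 116 per group by the normal approximation. The t-test version gives 116.93, so 117, as stated.
- At 125 per group the standard error is 10.6 × √(2/125) = 1.341. Power is Φ(3.9/1.341 − 1.960) = 0.829.

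**5. Power with crossover, on the planned analysis.** The article states: "The primary analysis for VFD-28 will use a cumulative logistic regression model to account for the ordinal nature of the endpoint". Power was therefore taken from that model under these assumptions:

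- Control VFD-28 has a point mass at 0 of 20%, 24%, 27% or 30%. The rest is a discretised beta distribution on 1 to 28, fitted so that the mean is 15.6 and the SD 10.6.
- Treatment is a proportional-odds shift giving +3.9 days (OR 2.00, 2.02, 2.06, 2.16 respectively).
- A share c of placebo patients receives the full treatment effect, so the placebo arm is (1 − c) × control + c × treated.
- There are 125 patients per arm and 3000 simulations of the fitted cumulative logit with a Wald test.

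| c | 20% zeros | 24% | 27% | 30% |
|---|---|---|---|---|
| 0 | 0.890 | 0.891 | 0.901 | 0.940 |
| 5% | 0.857 | 0.855 | 0.877 | 0.907 |
| 10% | 0.802 | 0.815 | 0.824 | 0.886 |

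Wilcoxon simulations (20,000 runs) agree closely. At c = 10% they give 0.804, 0.812, 0.831 and 0.874. They reach 0.80 at c = 10.3%, 11.5%, 13.3% and 18.7%, which is about 13 (0.103 × 125) to 23 (0.187 × 125) placebo patients. If crossovers gain only half the log odds ratio, Wilcoxon power at c = 10% is 0.848 to 0.910.

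**6. For reference, the difference-in-means basis.** The diluted difference is 3.9 × (1 − c). At c = 5% it is 3.705 days, with power Φ(3.705/1.341 − 1.960) = 0.789. At c = 10% it is 3.51 days, with power 0.745. This is less favourable, but it is not the planned analysis.

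**The case against.** The strongest case on the other side is that unrestricted care, with relevant drugs recorded and patients analysed as randomised, is a recognisable pragmatic choice, and that use is inferred rather than shown. Four points support it.

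- **Use may be rare.** Criteria for starting a spontaneous breathing trial ask for cardiovascular stability with little or no vasopressor. Patients recently given levosimendan are excluded. Trained clinicians know that the blinded infusion may already be levosimendan. This stands in part: the breathing-trial criteria are encouraged rather than mandatory, and patients may also enter through a failed extubation. No rate can be put on it either way.
- **The override leaves the decision with the same physician.** This stands. The clause discourages use and does not prevent it. What is new is the instruction for the study infusion, which the article lacks.
- **Pharmacokinetic samples can be handled already.** This largely stands. Affected samples can be found from the inotrope record, and a rule for excluding them belongs in a pharmacokinetic plan or SAP not shown here.
- **Monitoring, nurse SOPs and unblinding exist, and unseen SOPs may cover this.** They limit harm once noticed. An SOP could add guidance, but the published rule says affirmatively that nothing is restricted.

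A reader might infer that the trial is at risk of being underpowered, because the difference-in-means calculation falls below 80% by 5% crossover. The documents do not support that. They give no rate of use, and the planned ordinal analysis holds 0.80 at 10% under every shape tried.

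**Conclusion.** The gap is real and minor. The article permits non-study levosimendan in either arm after randomisation and gives no instruction for the blinded infusion when it is started. The main consequence is avoidable exposure above the planned maximum in the active arm, by a factor of 1.5 to 2 at the assumed non-study rates and only during overlap with a study infusion. A cleaner treatment contrast and cleaner pharmacokinetic data are secondary gains.

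The power figures rest on assumed zero shares, an assumed proportional-odds effect and an assumed crossover share. They show that the loss is probably small, with about 13 to 23 of 125 placebo patients needed to bring power down to 80%.

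Two further inferences should be resisted. Placebo-arm use would not be invisible, since inotropes must be recorded; it would simply not be flagged as a deviation. And an exception with a physician override would not guarantee the contrast.

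**What to change.** Add to the concomitant-care section:

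- Non-study levosimendan should be avoided from randomisation to day 28 unless the treating physician judges it clinically unavoidable.
- If it is given, stop any running study infusion and withhold the remaining ones.
- Record levosimendan by name, with dose and time, in the existing inotrope record.
- Log a protocol deviation and report use by arm.
- Keep the patient in the randomised arm for the primary analysis.

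All other concomitant care stays unrestricted, and emergency unblinding stays available on its present terms.

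The cost is one or two sentences and a line in site training, with no new data collection beyond the drug name, dose and time. There are two downsides. One is a small, overridable limit on prescribing one drug. The other is the loss of later study doses in the few affected patients, which in the active arm can itself slightly weaken the contrast. The sample size does not change.

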### Provisions for post-trial care

Not applicable. There is no need for provisions for post-trial care after the patient is discharged from the ICU.

### Outcomes

The primary endpoint of the study is the number of ventilator-free days and alive (VFD) at day 28 from randomisation. This is a composite endpoint combining both mortality and the duration of ventilation. In case of death, the subject will be assigned a value of 0 VFD. Day 0 will be defined as the day of randomisation.

Secondary outcomes include ICU mortality, VFD from randomisation up until day 90, safety endpoints such as hypotension (MAP <65 mm Hg), cardiac dysrhythmia (atrial fibrillation, ventricular arrhythmias), dyspnoea sensation, EQ-5D-5L questionnaire at baseline, 3 months and 12 months, reintubation rate, non-invasive support after detubation and pharmacokinetics of levosimendan up until 5 days.

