### Objectives

The primary objective of WEANing with LEvoSimendan Study (WEANLESS) is to determine the effect of intravenous levosimendan on the number of ventilator free days and alive (VFD) at day 28 after randomisation. This is a composite endpoint combining both mortality and the duration of ventilation. A patient who dies before day 28 will be assigned 0 VFD. Day 0 will be defined as the day of randomisation.

Secondary objectives include evaluating the effects of levosimendan on patient-reported outcomes, measured through daily dyspnoea scores and quality of life measured with the the EuroQol five-dimensional (EQ-5D-5L) questionnaire. The study will also investigate its impact on healthcare resource utilisation and intensive care capacity, assessed through reintubation rates, ICU readmission within 90 days, the need for non-invasive respiratory support, ICU length of stay and mortality. Furthermore, the pharmacokinetics of levosimendan and its metabolites will be analysed in a subset of study patients, with measurements taken up to 120 hours after infusion of the medication.

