### Participant timeline

The time points for enrollment, interventions and follow-up can be found in table 1.

**Table 1 T1:** Participant timeline

	Pretreatment						Follow-up
	Day −1	Day 0	Day 1	Day 2, 3, 4, 6	Day 8, 15, 22	Day 28	Day 90, 365
Enrolment							
Eligibility screening	X						
Baseline characteristics		X					
Informed consent*		X					
Randomisation		X					
Interventions							
EQ-5D-5L		X					X
Study medication†			X		X		
Baseline lab‡		X					
TDM levosimendan				X			
Dyspnoea scores			Daily from extubation up until day 28/ICU discharge				
Assessments							
Ventilation data			Daily				
Adverse events/safety endpoints			Daily				
Reintubation rate			Daily from extubation up until day 28/ICU discharge				
Life status, duration of ventilation, ICU and hospital admission						X	X

* Informed consent is obtained before randomisation.

† Patients will receive the study medication weekly until successful weaning or until the primary endpoint is reached, with a maximum of four doses administered.

‡ In baseline lab we will include NTproBNP as a marker of cardiac failure and in case of a female a pregnancy test.

ICU, intensive care unit; NT-proBNP, N-terminal pro b-type natriuretic peptide; TDM, therapeutic drug monitoring.

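### ICU mortality, and a reintubation count that appears to stop at ICU discharge, are observed over windows that treatment can shorten; fixed dates should replace them

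*Protocol article*

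**What the plan says.** **Mortality.** The Outcomes section reads "Secondary outcomes include ICU mortality, VFD from randomisation up until day 90". ICU mortality has no fixed date there, and no other mortality outcome is named apart from the ventilator-free-day composites. The Objectives section lists "the need for non-invasive respiratory support, ICU length of stay and mortality", with no ICU limit and no time point. The paragraph on healthcare resource utilisation, under the plans for outcome collection, also lists mortality without a limit. The statistical methods section adds that the components of VFD-28, "mortality rates and the duration of ventilation, will be described separately for both treatment groups".

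**Reintubation.** The Table 1 row gives the window as "Daily from extubation up until day 28/ICU discharge". For daily clinical parameters, the section on collection of outcomes says they "will be recorded daily until day 28 or ICU discharge". The Extubation section says the protocol "requires documentation of all reintubation events", with no end date. The Population section counts reintubation within 7 days as a failed extubation.

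**Expected effect and available data.** The Clinical trial rationale hypothesises that levosimendan shortens weaning, "ultimately leading to a reduced ICU length of stay and lower mortality rates compared with standard care". Table 1 has a row for "Life status, duration of ventilation, ICU and hospital admission", marked at day 28 and at days 90 and 365.

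**The concern.** An outcome observed only while the patient is in the ICU depends on two things: how often the event happens and how long the patient stays there. If the drug brings ICU discharge forward and does nothing else, the treated arm is observed for less time and shows fewer ICU deaths and fewer ICU reintubations. Blinding does not prevent this, because the difference comes from the end of the window and not from how events are judged.

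What is at stake is the reading of two secondary outcomes. A lower ICU mortality or reintubation rate could be reported as benefit when part or all of it reflects earlier transfer to the ward. The Discussion also relies on reintubation rates and ICU length of stay to separate early death from never being extubated. Mortality at a fixed date does that more directly.

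**Working it through.** No figure in the plan bears on this point. The only related calculation is the sample size, and it reproduces. 25% of 15.6 is 3.9 days. With SD 10.6, two-sided alpha 0.05 and 80% power, a t-test needs 116.93, so 117 per group as stated. The point leaves the 125 per group unchanged.

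**Step 1: where each window ends**

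| Outcome | One place | Another place |
|---|---|---|
| Mortality | ICU mortality, no date (Outcomes) | Mortality without ICU limit (Objectives; resource utilisation); component of VFD-28 by arm (statistical methods) |
| Reintubation | Day 28/ICU discharge (Table 1) | All events (Extubation); reintubation within 7 days defines failed extubation (Population) |

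The slash in Table 1 is not explained. The parallel wording for daily clinical data uses the word or, so the natural reading is that counting ends at ICU discharge for anyone who leaves before day 28. On that reading, a patient who leaves the ICU 2 days after extubation and is reintubated on day 5 meets the Population section's 7-day definition but falls outside the Table 1 window. ICU readmission within 90 days is itself collected, so the plan expects some patients to return.

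**Step 2: can treatment move the end of the window?** Yes, by the trial's own hypothesis of a shorter ICU stay.

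**Step 3: how large could the effect be?** The documents give no mortality, ICU-stay or reintubation rates. Every input below is an assumption, chosen to show a range.

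*ICU mortality.* Let the death hazard λ be the same in both arms and the same in ICU and ward, and let only the ICU discharge hazard μ differ. Then

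- λ = −ln(1 − day-28 mortality)/28
- μ = 1/(mean days to ICU discharge)
- ICU mortality = λ/(λ + μ)

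Example with day-28 mortality 25% and discharge at 14 days versus 14 − 3.9 = 10.1 days:

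- λ = 0.2877/28 = 0.01027
- control: 0.01027/(0.01027 + 0.07143) = 12.6%
- treated: 0.01027/(0.01027 + 0.09901) = 9.4%
- apparent risk ratio 0.75, true risk ratio 1.00

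The 3.9-day shift borrows the trial's target difference in ventilator-free days. The plan states no target for ICU discharge. Apparent risk ratios:

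| True day-28 mortality, both arms | 14 days, 2 earlier | 14 days, 3.9 earlier | 20 days, 2 earlier | 20 days, 3.9 earlier |
|---|---|---|---|---|
| 15% | 0.87 | 0.74 | 0.91 | 0.82 |
| 25% | 0.87 | 0.75 | 0.92 | 0.83 |
| 35% | 0.88 | 0.76 | 0.92 | 0.84 |

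*Reintubation.* Let the 7-day risk r after extubation be the same in both arms, with ρ = −ln(1 − r)/7 and mean ICU stay after extubation L. The share seen in the ICU is ρ/(ρ + 1/L) × (1 − exp(−7(ρ + 1/L))).

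| True 7-day risk, both arms | L 4 vs 3 days | L 3 vs 2 days | L 4 vs 2 days |
|---|---|---|---|
| 15% | 7.2% vs 6.0%, RR 0.83 | 6.0% vs 4.3%, RR 0.72 | 7.2% vs 4.3%, RR 0.60 |
| 25% | 12.3% vs 10.2%, RR 0.83 | 10.2% vs 7.4%, RR 0.73 | 12.3% vs 7.4%, RR 0.60 |

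In this model a count over a fixed window gives a risk ratio of 1.00 in every scenario, because the ICU discharge hazard drops out.

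**The case against.** The strongest reply is that the plan already handles most of this. Every death to day 28 scores 0 in the primary endpoint wherever it occurs, VFD to day 90 extends the horizon, and the mortality component of VFD-28 will be described by arm. Two sections list mortality without an ICU limit, and the Outcomes list is introduced as inclusive. This stands, and it limits the point to secondary outcomes. It does not repair the outcome actually named: describing a component of VFD-28 gives no day-90 mortality, and VFD-90 does not show death separately.

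On reintubation, the reply is that Table 1 is a collection timetable with an ambiguous slash, that the Extubation section asks for all events, and that reintubation rates are to be retrieved from patient records. This also stands in part. Closure at ICU discharge is the natural reading but is not stated outright. The conflict is itself a reason to fix the wording.

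On size, the inputs are assumed, and a shift of this kind would usually not reach significance. Take true mortality of 20% in both arms, with 90% versus 75% of deaths occurring in the ICU. ICU mortality then reads 18% versus 15%. With 125 per arm the standard error is √(0.18 × 0.82/125 + 0.15 × 0.85/125) ≈ 4.7 points, so z ≈ 3/4.7 ≈ 0.64. The concern is therefore bias in direction and estimate, not a likely false significant result.

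A reader might go further and infer that the trial misses ward deaths, or that harm after early discharge would be invisible. The documents do not support that: such deaths enter the primary endpoint to day 28, and life status is recorded at days 28, 90 and 365. Nor do they establish that reintubations at ICU readmission go unrecorded.

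**Conclusion.** The point holds for two secondary outcomes. ICU mortality, and reintubation as Table 1 appears to count it, are observed over windows that the drug is expected to shorten, so both could favour levosimendan with no true effect even if the plan is followed exactly. The size cannot be derived from the documents. The illustrative risk ratios of 0.74 to 0.92 and 0.60 to 0.83 rest on constant hazards, equal event hazards in ICU and ward, and assumed rates and stays. If ICU stay does not differ between arms, this bias does not arise. The primary endpoint, its analysis and the sample size are unaffected. Separately, the mortality and reintubation wording is inconsistent between sections and needs to be reconciled whatever the size of the bias.

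**What to change.** - **Outcomes section:** name all-cause mortality at day 28 and at day 90 as the secondary mortality outcome, taken from the life status already in Table 1. Keep ICU mortality as descriptive. Align the Objectives section and the resource-utilisation paragraph with this.
- **Table 1, reintubation row:** count reintubation from randomisation to day 28 regardless of ICU discharge, including reintubation at ICU readmission, consistent with the requirement to document all events.
- **Left to the SAP:** the denominator (all randomised or all extubated), death as a competing event, and the effect measure. A fixed end date removes the dependence on ICU discharge. It does not remove the fact that patients extubated earlier are at risk for longer, which belongs with the choice of denominator.

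The cost is a wording change and a short records check for reintubation after ICU discharge. The mortality outcome needs no new data, and the sample size stays at 250.
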